#### C-Reactive protein (CRP)

2.12.4.

High sensitivity CRP will be measured at the start of the study, end-of-treatment and follow up. Non-fasting venous whole blood will be sampled in an EDTA-tube analyzed on a clinical chemistry analyzer (Architect ci16200, Abbott Laboratories, Abbott Park, Illinos, USA) at Drammen Hospital to prevent inter-laboratory bias.

#### Interview guide

2.12.5.

An interview guide was developed for the qualitative part of the study by our inter-disciplinary research group.

### Sample size and power calculation

2.13.

Statistical power calculation was based on the primary outcome of HADS with subscale outcomes of HADS-depression and HADS-anxiety. A conservative anxiety/depression effect size from previous studies of individual and group ATT for depression was used (0.67). This effect size is similar to what has been reported in a meta-analytic study of CBT and other psychological treatments (0.67) (Cuijpers et al., 2010). Thus, based on previous research, we expected a difference between the two conditions (ATT and WLC) amounting to an effect size of approximately 0.67. Allowing for 15–20% drop out in accordance with previous studies, we aim for a final sample size of 32 in each group, i.e., 64 in total. This yields a statistical power above 90% using a two-sided significance test (*p* < 0.05).

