## Introduction

1.

Coronary heart disease (CHD) is one of the leading causes of death worldwide (Nowbar et al., 2019). Psychological distress such as significant symptoms of depression and anxiety are common in CHD patients (30–40%) (Reid et al., 2013) and commonly occur both immediate and longer periods of time after an acute cardiac event (Palacios et al., 2016). In an observational study from Norway, we reported prevalence rates of depression and anxiety of 14.7 and 21.1%, respectively, as assessed by the Hospital Anxiety and Depression Scale (HADS), mean 16.7 months after a CHD event (Frøjd et al., 2022b).

Patients with CHD have increased mortality risk with depression or anxiety alone being associated with up to two-fold increased risk of cardiovascular events and mortality (van Melle et al., 2004; Watkins et al., 2013). Depression and anxiety commonly co-occur and in those with both conditions, the prognosis is particularly poor with three-times increased risk of mortality (Watkins et al., 2013). Furthermore, associations between depression and anxiety have been reported for higher rates of cardiovascular risk factors, such as smoking and low physical activity, lower treatment adherence and higher levels of markers of immune function (Munkhaugen et al., 2018). The latter risk factor, more specific C-Reactive Protein (CRP), is an independent risk factor for recurrent cardiovascular events in CHD patients (Ridker et al., 2017). In addition, anxiety and depression symptoms are linked to poorer quality of life, higher rates of hospital admissions and work retention (Holdgaard et al., 2023).

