### Eligibility criteria

2.4.

Patients will be asked to participate in the study if they meet the following inclusion criteria:

Previously hospitalized with myocardial infarction and/or angiography-verified atherosclerosis.A score of ≥8 on the HADS-anxiety and/or depression subscales.Age ≥ 18 to ≤65 years.Ability to understand and speak the Norwegian language.Signed informed consent.

Patients will be excluded if they meet any of the following criteria:

Current or past neurological illness, traumatic brain injury.Current alcohol and/or substance dependency disorders.Psychotic disorders, bipolar disorders, developmental disorders or learning disabilities.Cognitive impairment which precludes informed consent/ability to participate.Acute suicidality.Life-expectancy less than 12 months.Concurrent psychological intervention for emotional distress.Antidepressant or anxiolytic medication initiated or changed during the past 8 weeks.

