#### Quantitative analysis

2.14.1.

A repeated measures linear mixed-model will be used to estimate treatment effects for the combined sample, with HADS-A and HADS-D scores as outcomes, from pre-treatment, post-treatment and 6 months follow-up. Controlled effect sizes will be calculated in the following way: post treatment for immediate ATT minus post waiting list divided by the pooled standard deviation. Both ITT and per protocol analyses will be reported.

The primary reported analyses will be carried out as an intention-to-treat with all randomized participants. The analysis is supplemented with per-protocol analyses defined by participation in ≥4 of the 6 group-based sessions. Missing information on other co-variates will be permitted if there is <20% missing data for the co-variate in question. Age, gender, HADS-D and HADS-A scores will be entered in the models as covariates if baseline differences are observed.

An estimate of treatment effect size will be derived by comparing the wait-list control and intervention group on levels of symptoms of anxiety and depression (HADS), rumination (RRS), worry (PSWQ), insomnia (BIS), metacognitive beliefs (MCQ-30, PBRS, NBRS) and inflammation (CRP) at baseline, end of treatment and 6 months follow-up. False discovery rate will be applied for multiple testing (Benjamini and Hochberg, 1995).

Analyses will be undertaken using Stata SE vs. 18.0 (StataCorp, 2023) and/or R (R Core Team, 2021) and conducted by a statistician who will remain blind to group allocation throughout. A detailed statistical analyze plan (SAP) will be prepared and published prior to analyses taking place.

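### Section 2.13 applies one effect of 0.67 to both HADS subscales in an either-subscale population; it is not shown to be conservative, least of all for HADS-D, and 32 per arm does not give the stated power

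*Protocol article*

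**What the plan says.** The protocol article's section on sample size and power calculation (2.13) fixes one effect for two outcomes. "Statistical power calculation was based on the primary outcome of HADS with subscale outcomes of HADS-depression and HADS-anxiety". The effect is described as follows: "A conservative anxiety/depression effect size from previous studies of individual and group ATT for depression was used (0.67"). A second support is offered: "This effect size is similar to what has been reported in a meta-analytic study of CBT and other psychological treatments (0.67"). The comparison sized is between arms: "we expected a difference between the two conditions (ATT and WLC) amounting to an effect size of approximately 0.67". With 32 per arm, 15–20% dropout and a "two-sided significance test (*p* < 0.05"), the section states power above 90%.

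The eligibility criteria (2.4) ask for "A score of ≥8 on the HADS-anxiety and/or depression subscales". The quantitative analysis (2.14.1) plans a repeated-measures mixed model "with HADS-A and HADS-D scores as outcomes", with intention-to-treat on all randomised participants as the primary analysis. Neither subscale's analysis is restricted to patients who qualified on that subscale.

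The Introduction reports, from the group's earlier Norwegian CHD study, "prevalence rates of depression and anxiety of 14.7 and 21.1%, respectively".

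**The concern.** A patient can enter on anxiety alone with a HADS-D score in the range that section 2.12.1 calls normal (0 to 7), and the reverse. Such a patient has less room to improve on the subscale that did not qualify them, yet counts fully in its analysis. If 0.67 describes patients who have the symptom being treated, the average effect in this mixed population would be smaller. The loss would be larger for HADS-D, because depression was the rarer of the two in the group's own cohort. Section 2.13 makes no allowance for this and calls the figure conservative.

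The stated power is also too high for the stated inputs before any dilution. A reader who trusts both statements could take a non-significant HADS-D result as firmer evidence against ATT than this design can supply.

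**Working it through.** **Inputs.** From section 2.13: d = 0.67, 32 per arm, two-sided 5%, dropout 15–20%. From the Introduction: depression 14.7%, anxiety 21.1%. Assumptions: those rates use the cut-off of 8 given in section 2.12.1, and the eligible patients resemble that cohort.

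**Step 1. The plan's own figure.** For a two-sample t test the noncentrality is d·√(n/2) = 0.67 × √16 = 2.68, with 62 degrees of freedom. Power is 75.1%. The normal approximation gives Φ(2.68 − 1.96) = Φ(0.72) = 76.4%. The stated figure above 90% is not reproduced.
- If dropout comes out of the 32, about 27 (15%) or 26 (20%) remain per arm, and power is 68% or 66%.
- 90% power at 0.67 needs 48 per arm. With 32 per arm it needs d of about 0.82.
- With baseline adjustment the effective d is 0.67/√(1 − r²). Power then reaches 90% at 32 per arm only if the baseline correlation r is at least about 0.58 (about 0.68 at 26 per arm). Section 2.13 states no such correlation.

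**Step 2. Share at or above 8 on each subscale among eligible patients.** Eligible means elevated on either subscale, so the share is the subscale's rate divided by the rate of either.
- No overlap: the rate of either is 14.7 + 21.1 = 35.8%. HADS-D share 14.7/35.8 = 41%; HADS-A share 21.1/35.8 = 59%.
- Full overlap (every depressed patient also anxious): the rate of either is 21.1%. HADS-D share 14.7/21.1 = 70%; HADS-A share 100%.

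The share starting below 8 is therefore 30% to 59% on HADS-D and 0% to 41% on HADS-A.

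**Step 3. Simple dilution.** Let s be the share from step 2 and f the gain below 8 as a fraction of the gain at or above 8 (assumed). Then d = 0.67 × [s + f(1 − s)], with the SD held fixed. For example, HADS-D with no overlap and f = 0.5: 0.67 × [0.411 + 0.5 × 0.589] = 0.473. Power is for 32 per arm, two-sided t test, no baseline adjustment.

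| Subscale | Overlap | s | d, f = 0 | Power | d, f = 0.5 | Power |
|---|---|---|---|---|---|---|
| HADS-D | none | 41% | 0.275 | 19% | 0.473 | 46% |
| HADS-D | full | 70% | 0.467 | 45% | 0.568 | 61% |
| HADS-A | none | 59% | 0.395 | 34% | 0.532 | 55% |
| HADS-A | full | 100% | 0.67 | 75% | 0.67 | 75% |

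With f = 1 and a fixed SD there is no dilution, and both subscales have 75%.

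**Step 4. Effect of using baseline.** Take r = 0.5 as an illustration and divide each d by √(1 − 0.25) = 0.866. The undiluted power rises to 86.1%. HADS-D power becomes 24.0% to 56.5% with f = 0 and 57.5% to 73.4% with f = 0.5. Baseline use therefore helps, but it raises the undiluted reference too, so the gap between them remains.

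**The case against.** The strongest reply has four parts.

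*The source populations are unknown.* Section 2.13 calls 0.67 an anxiety/depression effect, does not describe who was enrolled in the source studies, and cites a meta-analysis of psychological treatments in support. A reader might infer that 0.67 is known to come from patients selected for the target symptom. The document does not show that; it is an inference from the words about depression. This part stands. It does not rescue the description as conservative, since nothing shows that the figure fits an either-subscale population.

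*Dilution is not established.* A reader might infer that both subscales are certainly diluted. Under full overlap HADS-A is not diluted at all, and the loss on HADS-D depends on the gain below 8. The prevalences come from an observational cohort, not from the consenting, re-screened sample. This also stands, so the result is a range and not an estimate.

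*The planned model uses pre-treatment scores.* Power computed from post-treatment scores alone understates the planned analysis. A simulation using baseline illustrates this. It matches the subscales to the two prevalences with assumed means of 4.7 and 3.9, and assumes a between-subscale correlation of 0.5–0.7 and a noise SD of 3. It gives HADS-D power of about 31%–36% with no gain below 8 and about 60%–62% with half gain. A reader might conclude that a null HADS-D result is likely even if ATT works as assumed; on these figures that holds only in the no-gain case.

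*Separate subscales are a legitimate choice.* One might infer that the HADS total should become primary, because every participant is elevated on at least one component. The documents do not require that. The trial addresses anxiety and depression separately and plans false discovery rate control. The total's advantage shrinks if noise on the two subscales is correlated, and a change of primary outcome during recruitment has a real cost.

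**Conclusion.** The point holds in limited form. Section 2.13 carries one effect over to two subscales in a population where, on the group's own rates, 30% to 59% would start below 8 on HADS-D and 0% to 41% on HADS-A. The description as conservative is unsupported, most clearly for HADS-D, whose qualifying share is the lower of the two whatever the overlap.

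Two levels of certainty should be kept apart. The shortfall at the stated inputs follows from section 2.13 alone: about 75% at 32 per arm and 66% at 26, not above 90%, unless a baseline correlation that the section does not state is assumed. The further loss on HADS-D is conditional. Without baseline adjustment, power is 19% to 45% with no gain below 8 and 46% to 61% with half gain; it is higher under the planned model. These figures assume that the cohort rates apply to the eligible patients, that 0.67 is the effect at or above 8, and that the SD is unchanged by the mixture.

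**What to change.** In section 2.13, remove the word conservative and the claim of power above 90%. For each subscale state:
- the expected share of participants at or above 8 at entry, with the overlap assumed;
- the effect assumed in the either-subscale population, and how it follows from 0.67;
- the resulting power over a stated range of these assumptions, for the planned baseline-using mixed model, with its assumed correlation and the number expected to be analysed after dropout.

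Keep HADS-A and HADS-D as the primary outcomes. The HADS total, a sum of items already collected, may be added as a supportive analysis.

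This changes wording and calculation only: no new data, no new patients and no change of primary outcome. The downside is that the stated power becomes less favourable, particularly for HADS-D.

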**Methods:**

ATT-CHD is a randomized wait-list (WL) controlled study. Eligible CHD patients from two hospitals with Hospital Anxiety and Depression Scale (HADS)-Anxiety and/or HADS-Depression subscales scores ≥8 will be randomized into ATT (*n* = 32) or WL control (*n* = 32). After 6–8 weeks, WL patients will be allocated to ATT. Participants will be evaluated pre-, mid- and post-treatment, and at 6-months follow-up using changes in HADS as primary outcome. Secondary outcomes will be changes in psychiatric disorders, rumination, worry, type D-personality, metacognitions, insomnia, quality of life, and C-Reactive protein (CRP).

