Consequently, the most recent European Society of Cardiology guidelines on CVD prevention recommends assessments of psychological needs, including screening for anxiety and depression (Visseren et al., 2021). The importance of assessments of psychological distress in CHD and further intervention have been strongly emphasized (Thompson and Pedersen, 2023). However, a recent Cochrane review of studies on available drug and psychological treatments have showed only small effects on such symptoms and quality of life, and no effect on cardiac prognosis (Richards et al., 2017). Indeed, Richards et al. (2017) found no specific psychological intervention recommendable, and only small improvements in the interventions tested. More recently, Wells and colleagues reported metacognitive therapy (MCT) as a promising group delivered treatment in reducing psychological distress and improving quality of life in cardiac rehabilitation patients an evaluated their MCT interventions in cardiac patients (Wells et al., 2021, 2022a,b). Another recent multicenter RCT on cognitive-behavior therapy (CBT) in cardiac rehabilitation (CR) patients found that supplementing CBT to CR could improve anxiety, depression, quality of life as well as cardiac readmissions (Holdgaard et al., 2023). These effects were maintained at 6-months follow-up.

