### Trial status and timeline

2.17.

The first patient was randomized November 30th 2022 and per May 2023 10 out of 64 patients have been included and followed-up. A conservative estimate is that all 64 patients may be enrolled over a 2 year period. Thus, the final results of primary endpoint are expected in December 2024.

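### The stated power of above 90% does not follow from its inputs: d = 0.67 with 32 per arm gives 75%, and about 66–68% on complete cases after the planned dropout

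*Protocol article*

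**What the plan says.** Section 2.13 of the protocol article (Sample size and power calculation) bases power on the HADS subscales. It gives the effect as a contrast between arms: "we expected a difference between the two conditions (ATT and WLC) amounting to an effect size of approximately 0.67". After allowing for 15–20% dropout it continues: "we aim for a final sample size of 32 in each group, i.e., 64 in total". The result follows directly: "This yields a statistical power above 90% using a two-sided significance test", with p < 0.05 as the threshold.

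Three other places bear on how to read this:

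- The Methods paragraph of the abstract says that patients "will be randomized into ATT (*n* = 32) or WL control (*n* = 32"), so 32 per arm is the number randomised. Section 2.17 (Trial status and timeline) agrees: "A conservative estimate is that all 64 patients may be enrolled over a 2 year period".
- Section 2.14.1 (Quantitative analysis) defines the controlled effect size as "post treatment for immediate ATT minus post waiting list divided by the pooled standard deviation". This is the ordinary two-sample standardised difference.
- The same section plans a repeated-measures linear mixed model on all randomised participants. Baseline HADS enters as a covariate only if baseline differences are seen. No pre–post correlation is given anywhere in the article.

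**The concern.** Section 2.13 gives every input that a two-sample power calculation needs, and the printed result is about 15 percentage points higher than those inputs yield. The calculation names no test, model or correlation that would close the gap.

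The figure describes the primary outcome. Someone told that power is above 90% will take the chance of missing a true effect of 0.67 to be below 10%. For an unadjusted comparison of post-treatment scores it is 25% with everyone analysed and 32–34% after the planned dropout. That changes how much weight a non-significant result can bear.

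**Working it through.** **Inputs.** d = 0.67 between arms (section 2.13), scaled as post-treatment difference over pooled SD (section 2.14.1). Two-sided alpha 0.05 (section 2.13). 32 per arm randomised (abstract; section 2.17). Dropout 15–20% (section 2.13).

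**Step 1: try to reproduce the stated figure.** For n per arm, the noncentrality parameter is d × √(n/2) on 2n − 2 degrees of freedom. Power is the probability that a noncentral t with that parameter falls beyond the two-sided 5% critical value.

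At n = 32: 0.67 × √16 = 2.68, 62 df, critical value 1.999, power **75.1%**. The normal approximation gives Φ(2.68 − 1.96) = Φ(0.72) = 76.4%. The stated figure is not reproduced.

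Variants close to the text do not reach it either:

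- One-sided 5% at 32 per arm: 84.3%.
- 38 or 40 per arm (32 inflated for 15% or 20% dropout): 82.2% or 84.1%.

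**Step 2: apply the planned dropout.** 32 × 0.85 = 27.2 and 32 × 0.80 = 25.6, so about 27 and 26 per arm have post-treatment data.

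| Analysed per arm | Noncentrality | Power (t) | Power (normal) |
|---|---|---|---|
| 32 | 2.680 | 75.1% | 76.4% |
| 27 | 2.462 | 67.6% | 69.2% |
| 26 | 2.416 | 65.9% | 67.6% |

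**Step 3: what 90% would need.** At d = 0.67, 80% power needs 36 analysed per arm and 90% needs 48 (t-test). Turned round, the effect detectable with 90% power is 0.82 at 32 per arm, 0.90 at 27 and 0.92 at 26.

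**Step 4: can the planned model rescue the figure?** Adjusting for baseline with pre–post correlation r multiplies the residual variance by 1 − r², so the effective effect is 0.67/√(1 − r²). Setting this equal to the detectable effects in step 3 gives the correlation required:

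- 32 per arm: 1 − r² = (0.67/0.823)² = 0.66, so r is about 0.58.
- 27 per arm: (0.67/0.899)² = 0.555, so r is about 0.67.
- 26 per arm: (0.67/0.917)² = 0.534, so r is about 0.68.

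A change-score contrast has variance factor 2(1 − r). At 32 per arm it needs r of about 1 − 0.66/2 = 0.67.

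Baseline-adjusted power for assumed correlations (none is stated in the article):

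| Assumed r | 32 per arm | 27 per arm | 26 per arm |
|---|---|---|---|
| 0.5 | 86% | 80% | 78% |
| 0.6 | 91% | 86% | 84% |
| 0.7 | 96% | 92% | 91% |

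**The case against.** The best defence is that section 2.14.1 does not plan a post-only t-test. It plans a repeated-measures mixed model that includes the pre-treatment score, and such a model can exceed 90% at 32 per arm. This stands, and it limits the finding. The power of the planned analysis cannot be determined from the article, so 75% is what the stated inputs give and not a proven figure for the primary analysis. It does not rescue the sentence in section 2.13, which gives no correlation or model, while section 2.14.1 makes baseline covariate adjustment conditional.

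A related defence is that the primary analysis keeps all randomised patients, so 26–27 per arm is not the number analysed. That is right as to the model. But a patient without a post-treatment score adds little to the post-treatment contrast, so 66–68% is a fair complete-case illustration and should be labelled as one.

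The documents do not support four stronger readings that a reader might infer:

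- *That the dropout allowance is not real.* 27/0.85 = 31.8 and 26/0.80 = 32.5, both about 32. The 64 randomised can already contain the allowance. What does not fit is the power figure; the word final merely leaves it unclear whether 64 is counted before or after dropout.
- *That the figure came from a paired, within-group test.* Such a test gives 91–92% with 26–27 patients, but other routes also exceed 90%: 64 per arm (96%), some repeated-measures ANOVA set-ups with f = 0.67/2 = 0.335, or an unstated correlation. Nothing in the article shows which was used.
- *That 0.67 is not conservative.* The Introduction reports "only small effects on such symptoms and quality of life", but of other drug and psychological treatments, and it goes on to more favourable recent results in cardiac rehabilitation. Section 2.13 ties 0.67 to earlier ATT studies and a meta-analysis that are not at hand.
- *That the false-negative risk of the primary analysis is 25–34%.* This holds for the unadjusted comparison only.

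**Conclusion.** The concern holds: power above 90% does not follow from the inputs printed in section 2.13. With d = 0.67, a two-sided 5% test and a two-sample comparison, power is 75% with 32 per arm analysed and about 66–68% with the 26–27 per arm left after 15–20% dropout on a complete-case basis. The normal approximation moves these by only 1 to 2 points.

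A figure above 90% is attainable under the planned type of model if the pre–post correlation is about 0.58 or more with no dropout, or 0.67–0.68 or more with the planned dropout. The article neither states nor justifies such a value. These figures take 0.67 on the scale defined in section 2.14.1 and address one HADS subscale at a time. They make no allowance for testing two subscales or for clustering within therapy groups, either of which would lower power further.

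**What to change.** Keep 64 patients and correct the statement in the SAP and the results paper, in one of two ways:

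1. Restate the power, for example: *With 32 per arm analysed, power is 75% for d = 0.67 (two-sided 5%, two-sample comparison); with 15–20% dropout (26–27 per arm with post-treatment data) it is about 66–68%. The effect detectable with 90% power is 0.82, or 0.90–0.92 after dropout.*
2. If the claimed figure rests on a model that uses baseline HADS, name that model, state the assumed pre–post correlation and its source, give power with and without dropout, and make the use of baseline in the analysis unconditional so that it matches the calculation.

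In either case, say plainly that 64 is the number randomised, before dropout.

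The cost is wording and a less favourable stated power. No extra patients or design change are needed; option 2 also requires the handling of baseline HADS to be settled in the SAP before analysis.
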